**Fig. 1 Fig1:**
[figure not shown]
Participant recruitment process

#### Detailed description of the intervention modes

Three modes of intervention and one control group are proposed for this study. The three intervention modes are:Intervention 1: Healthy Kiosk and nutritional education (KSEAN);Intervention 2: Optimized physical activity (AFSO);Intervention 3: Healthy Kiosk and nutritional education (KSEAN) + Optimized physical activity (AFSO).

Each component of the intervention modes is described below:Nutritional Education Intervention: This intervention is based on the “Social Cognitive Learning Theory”, which incorporates the interdependency relationship between personal characteristics, behavioural factors and environmental influences [31]. Teachers will provide knowledge and skills in relation to choosing healthy foods at school and at home by providing learning material. Year one to year four students participating in the programme will work with learning material based on the dietary guidelines for the Chilean population that provides nutritional concepts that are reinforced with theory and practical activity, along with the creation of healthy messages [32]. To enhance the effectiveness, the nutritional education activities will be scheduled over 16 sessions of 90 min each. As this is not part of the curriculum, the teacher in charge of each teaching unit (UTP), at each individual school, will define the time when this content will be presented to the students. The implementation of the learning material, including teacher interviews and display of the work conducted by the children in wall displays, will be supervised by a nutritionist, who is part of the research team.Healthy Kiosk Implementation: The model described by Bustos and colleagues in the *Manual de Implementación de un Espacio y Punto de Venta Saludable en Escuelas Básicas de Chile* [33] will be replicated in this study. This considers the following:The construction of a Healthy Space, located within the school. This space is defined as a place that will encourage healthy lifestyles by promoting recreational activities, the sale of healthy foods and the implementation of various educational strategies aimed at modifying and strengthening healthy behaviour amongst schoolchildren. The Healthy Space will consist of a healthy kiosk, surrounded by tables, chairs and a number of games of an attractive design and painted in bright colours. The kiosk will be built in accordance with what is established in the “Reglamento Sanitario de los Alimentos” [34] and its design will promote the visibility of the food that will be displayed in refrigerated display cases and shelves inside the kiosk.The food offering will consist of avocado and fresh cheese or tomato sandwiches, fat-free yoghurt and milk, milk-based desserts, jelly, sugar-free biscuits, cereals, fresh and dried fruits, sugar-free juices and drinks, mineral water and other snacks low in calories. Processed foods will be determined to be low in calories if the nutritional information on the packaging shows the portion sizing and the nutritional information per portion and if this does not exceed 130 Kcal, 3 g of total fats, 20 g of carbohydrates and 140 mg of sodium. For fruits and vegetables a standard portion of 150 g is considered acceptable, as is 30 g for nuts. Also, it will be established that dairy products must be fat-free or low in fat and that other drinks must be sugar-free [33].Strategies for promoting the sale of healthy foods and processed foods low in calories will be established based on behavioural economics, which places the food recommended by the Chilean Dietary Guidelines, such as fruits, vegetables and dairy products, amongst others, in the most visible place within the kiosk. Alongside this, positive reinforcement statements promoting the benefits of consuming healthy foods will be displayed to promote their sale. Also, the kiosks will be fitted with an information board displaying various themes related to the promotion of a healthy lifestyle and a price list of foods available for purchase.Training will be provided for the kiosk staff in topics such as healthy eating, how to read and understand the nutritional information displayed on food packaging, hygiene, food preparation and handling, and communicational and marketing strategies for promoting the sale of healthy foods.
Physical Activity Intervention: The optimized physical education classes will consider what is already established in the curriculum for the subject physical education and health, with four teaching hours per week, distributed in blocks of 90 min each on different days of the week. Each school selected for this mode of intervention will have a specialized physical education teacher or a teacher with specific training in physical education. Teachers will receive further training to ensure: 1) that the effective class time has a duration of 70 min; 2) that 50% of the effective time consists of activities that demand a moderate to vigorous intensity. Monitoring will be carried out of all of the physical education classes conducted for years 1 to 4, by external physical education teachers that have been previously trained and standardized. They will measure the effective class time and will select children at random to wear the pedometers during the class.

#### Possible adverse effects of the physical activity intervention

A register will be designed and implemented to identify any potential adverse effect on the children taking part in the intervention that could occur as a result of the increase in physical activity from moderate to vigorous. An injury management protocol will also be designed and provided. With regard to nutritional education, a form will be designed to identify the causes for not complying with the planned activities.

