## Methods

### Design

The proposed study is a cluster randomized controlled trial to evaluate the effect of a school-based intervention in nutritional education and physical activity over two school years in children aged between 6 and 10 years, attending primary public schools. Three modes of intervention will be implemented and the results will be measured alongside those of a control group. The intervention modes consist of the following:Intervention 1: Healthy Kiosk and nutritional education (KSEAN);Intervention 2: Optimized physical activity (AFSO), where the physical education classes will be taken by a specialized physical education teacher or a primary teacher with a specialization in physical education. The effective class time will be a minimum of 70 min, during which half of the time should involve undertaking activities of moderate to vigorous intensity;Intervention 3: Healthy kiosk and nutritional education (KSEAN) + Optimized physical activity (AFSO);Control group: Physical education classes will follow the curriculum as indicated for the subject of physical education and health (AFS).

The study will be conducted in 12 clusters (schools) in three regions of Chile (VIII, VI and Metropolitan), distributed in four schools per region, randomly assigned to KSEAN, AFSO, KSEAN+ AFSO or control.

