Parents will be informed that this study will determine the nutritional status of each child by measuring weight, height, skinfolds and waistline. These measurements only require that the children remove their shoes and any other heavy element that they might be carrying. It will also be indicated that they will need to answer a survey aimed at determining their current dietary behaviours and that the children’s fitness levels, along with the intensity of the activities conducted in the physical education classes, will be determined by conducting the following tests:Grip strength: consists of squeezing a dynamometer with both right and left hands. This instrument measures the grip strength of the child [29].Measuring the distance of a jump done with both feet together and without a run-up [29].Measuring the intensity of the physical activity by using a pedometer [30], which is a portable device used to count steps that will be placed on the waist of children and secured with a belt while they participate in the physical education classes.

It will be indicated to the parents that all of these tests will be conducted under the supervision of a qualified physical education teacher with experience in conducting all of the tests along with a teacher from the school. It will also be explained that all of the tests should take approximately 15 min to complete and that these will be conducted at the beginning and end of the school year during class time. The only measurement that will be taken throughout the whole year is the intensity of the physical education class. The child’s nutritional status will be informed by means of a letter addressed to the parents.

It will also be indicated that the participation in this study is voluntary and that a child can choose to stop participating at any moment. Additionally, it will be made clear that the participation in this study will not incur any cost for the families of the children nor the school, and that all of the information collected will be kept confidential and will only be used for this study.

The diagram shown in Fig. 1 below, shows the flow of the suggested recruitment process for this study:

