#### Control group

The participants in this group will participate in physical education classes that follow the specifications of the physical education and health curriculum as indicated by the Education Ministry. They will not participate in nutritional education classes and a healthy kiosk will not be implemented at their school. The control group participants will be provided with the same level of support and information, and will be subject to the same evaluations as the participants of the intervention groups in this study.

At the end of the study all of the participants will be invited to take part in nutritional education talks and all participating schools will have the infrastructure of their kiosks repaired. In parallel, teachers from all participating schools will be provided with training in nutritional education and optimized physical education classes.

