### Data collection

#### Baseline data collection

During the baseline evaluation, participating children will be interviewed by the field personnel, who have been previously trained for this task. The evaluation is to take place at each participating school, following prior authorization by the relevant municipal authorities and school principals.

The following information will be registered.General information about each participant: name, class, gender, RUT (national ID number), and whether the participant receives benefits under the nutritional school programme and/or the social protection programme. These are government programmes that provide benefits to persons, families or territories that are classed as being in a vulnerable situation [37].Anthropometry: weight, height, skinfolds (biceps, triceps, subscapular, suprailiac).Fitness level: dynamometry of right and left hand to measure the isometric strength of the upper body, and length of jump with feet together to measure the explosive strength of the lower body.Duration of moderate to vigorous physical activity during physical education classes.A report of the nutritional knowledge and habits regarding the consumption of dairy products, fruits, vegetables, water, legumes, fish and snacks.A report detailing the main types of food purchased at the school kiosk and the amount of money spent.Food offering at the school kiosk: identification of the types of food and their macronutrient contribution.Number of street food carts/stalls that can be found outside the school and their distance in metres from the main school access.

All of the above evaluations will also be conducted after 8 months of intervention (before starting the summer holidays), after 12 months of intervention (return from summer holidays) and after 20 months of intervention (at the end of the second school year).

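### As worded, the adverse-effect register would describe events in the AFSO schools but give no between-arm comparison of injuries

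*Protocol article*

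**What the plan says.** The section on possible adverse effects of the physical activity intervention opens with "A register will be designed and implemented to identify" and then gives the target: "any potential adverse effect on the children taking part in the intervention that could occur as a result of the increase in physical activity". The same section promises an injury management protocol and, for nutritional education, a form on reasons for not carrying out planned activities.

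The Control group section says that control children "will participate in physical education classes that follow the specifications of the physical education and health curriculum" and "will be subject to the same evaluations as the participants of the intervention groups". Under Baseline data collection the article lists what is recorded and adds: "All of the above evaluations will also be conducted after 8 months of intervention", with further rounds at 12 and 20 months. Under Recruitment of participants, parents are told: "The only measurement that will be taken throughout the whole year is the intensity of the physical education class".

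The Design section describes 12 schools, "distributed in four schools per region, randomly assigned to KSEAN, AFSO, KSEAN+ AFSO or control".

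**The concern.** The register's definition does two things. It names its population as children taking part in the intervention, and it names its event as an effect that could follow from the increase in activity. Control children follow the usual curriculum, and KSEAN-only children receive the kiosk and nutritional education. Neither group is assigned more vigorous classes, so an injury in one of their classes does not fit the definition, even if the form happened to be available there.

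Children can also be hurt in ordinary physical education. A count from the AFSO-containing modes alone has no concurrent background rate beside it: an ordinary rate could look like harm, or a real excess could be dismissed as normal. Tying the event to the added activity also lets the recorder's view of cause affect what is entered. The trial means to advise authorities on which strategies to prioritise, and comparative harm bears on that advice. Randomisation already supplies the comparison group, and events not recorded at the time are hard to recover later.

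**Working it through.** The main check is a reading of the sections against each other, since the article gives no injury rate, safety margin or safety sample size to reproduce.

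**Step 1: who the register covers.** The heading refers to the physical activity intervention, the population is the children taking part, and the event is tied to the increase in activity. That points to AFSO and KSEAN + AFSO. Control and KSEAN-only are not named.

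**Step 2: whether the equal-evaluations sentence extends it.** The items listed under Baseline data collection are general information, anthropometry, fitness, duration of moderate to vigorous activity, nutritional knowledge and habits, kiosk purchases, kiosk food offering and street stalls. None is an injury or adverse effect. The statement to parents names class intensity as the sole year-round measurement. So the Control group sentence does not clearly reach the register. These lists omit the register for every arm, however, so they do not prove that controls are excluded.

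**Step 3: whether a comparison group exists.** Each of the four modes has one school in each of three regions, so 4 × 3 = 12 schools. Two modes contain AFSO (2 × 3 = 6 schools) and two do not (6 schools).

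**Step 4: what a common register could show.** This is illustrative only. Inputs: 1923 children recruited (Recruitment status); an equal split between AFSO-containing and other modes (assumed), 1923 / 2 ≈ 961 per side; injury risks over the two school years of 2%, 5% and 10%, equal on both sides (assumed). With e events on each side:

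SE(log RR) = √(2/e − 2/961), and the 95% CI is exp(±1.96 × SE) around a risk ratio of 1.

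| Assumed risk | e per side | SE(log RR) | 95% CI for RR |
|---|---|---|---|
| 2% | 19 | √(0.1053 − 0.0021) = 0.321 | 0.53 to 1.88 |
| 5% | 48 | √(0.0417 − 0.0021) = 0.199 | 0.68 to 1.48 |
| 10% | 96 | √(0.0208 − 0.0021) = 0.137 | 0.76 to 1.31 |

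Children are treated as independent here. With six schools per side, any positive within-school correlation widens every interval.

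**The case against.** The strongest reply is that the article neither uses the word only nor expressly excludes control children. The register is still to be designed, and a journal article may leave its sites and forms to the full protocol. Equal evaluations are promised to controls without restriction, and the baseline list is a poor guide because an event register would not appear there for any arm. No hypothesis, outcome or planned analysis concerns safety. The register stands next to an injury management protocol, which suggests child protection rather than estimation of a rate. The wording on potential effects that could occur is broad and need not demand a causal judgement before an entry is made. Finally, even a common register would give a wide interval.

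Much of this stands. A reader might infer that injuries cannot be compared between arms at all, or that the trial cannot judge the safety of AFSO. The documents support neither. The exclusion of controls is inferred, the final form of the register is not shown, safety is not a declared aim, and events in AFSO schools can still be described.

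What remains is that the article does more than stay silent: it states a population and an event, and both point away from the non-AFSO schools. If the sponsor does mean the equal-evaluations promise to include the register, the two sections need to be reconciled, and the same rewording does that. Imprecision is a reason to keep the comparison descriptive. It is not a reason to collect one side only.

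**Conclusion.** The point holds in a limited form. Followed as written, the register would yield a description of events in the six AFSO-containing schools, partly shaped by presumed cause, with no concurrent figure from the other six. What is lost is the between-arm comparison. The primary outcome and the trial's stated hypotheses are unaffected.

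The conclusion rests on reading the register section as a definition, and on the equal-evaluations sentence not clearly overriding it. It does not depend on the injury risks, which are assumptions. Those figures show only what a common register could offer: at 5%, the data would be compatible with anything from roughly a one-third reduction to nearly a 50% excess, before clustering is counted. The comparison would add context to the harm data but would often not settle whether AFSO raises injury risk.

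**What to change.** Reword the section on possible adverse effects so that:

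- one register runs in all 12 schools;
- it records every injury or adverse event in a physical education class, regardless of presumed cause;
- the event definition, the type of recorder and the procedure are the same in every mode;
- events are summarised descriptively by mode, with the AFSO-containing modes set against the other two and clustering by school allowed for.

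State in the Control group section that the register applies there too.

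The requirement for the same recorder matters. The article describes trained external monitors under the physical activity component. If they fed the register in AFSO schools while class teachers did so elsewhere, detection would differ by arm and the comparison could be biased.

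The cost is extra form-filling in the six non-AFSO schools, plus whatever is needed to provide the same type of recorder there. Only data capture changes; the handling of injuries is untouched.

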#### Control group

The participants in this group will participate in physical education classes that follow the specifications of the physical education and health curriculum as indicated by the Education Ministry. They will not participate in nutritional education classes and a healthy kiosk will not be implemented at their school. The control group participants will be provided with the same level of support and information, and will be subject to the same evaluations as the participants of the intervention groups in this study.

At the end of the study all of the participants will be invited to take part in nutritional education talks and all participating schools will have the infrastructure of their kiosks repaired. In parallel, teachers from all participating schools will be provided with training in nutritional education and optimized physical education classes.

### Outcome measures

#### Healthy Kiosk with nutritional education and optimized physical activity intervention (KSEAN + AFSO)

##### Primary result variable

Nutritional status of the participants after a 2-year intervention.

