##### Operational definition of nutritional status

Obese >2 Z of BMI, Overweight >1 Z of BMI, Normal ≥ − 1 y ≤ 1 Z of BMI.

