##### Optimized physical activity (AFSO) primary dependent variable

Fitness as measured in the lower body by the distance, in centimetres (cm), of a jump done with both feet together and without a run-up, and in the upper body by a dynamometer, which measures the isometric force in kilograms (kg) of the upper body by participants squeezing the instrument with the right and left hand.

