#### Healthy Kiosk with nutritional education intervention (KSEAN)

##### Primary dependent variable

Intake of foods measured as consumed and not consumed.

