##### Determination of sample size

The sample size was determined as that required to obtain a standard size of the effect of 0.2 on the BMI z-score, based on a previous nutritional and physical education intervention study conducted in primary schools to prevent childhood obesity by Kain et al. in order to identify this effect in four clusters per intervention mode, with a power of 0.8, a significance of 5% and an inter-cluster coefficient of variance of 0.00012 [35], 140 children per cluster are required along with a minimum of 11 clusters, giving a total of 1540 children. Given that this study was conducted in three regions and that each intervention mode must be conducted in each region, a total of 12 clusters and 1680 subjects are required. Assuming a participation loss of 10% in 2 years of intervention, the total sample size would be 1848 children.

It is anticipated that the grip strength dependent variable will be improved by 20% compared to the study conducted by Rojas C et al. [36]. With the sample size calculated in this manner, in order to have a power of 0.8 at a 95% confidence level, 130 subjects per cluster are required, thereby reaching a total of 1560 children between year 1 and year 4.

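### The primary variable is a set of BMI-z categories, but the stated 80% power is for continuous BMI z-score and does not carry over to those categories

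*Protocol article*

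**What the plan says.** All references are to the protocol article.

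- Under Outcome measures, the primary result variable for KSEAN + AFSO is "Nutritional status of the participants after a 2-year intervention". The operational definition that follows is purely categorical: "Obese >2 Z of BMI, Overweight >1 Z of BMI, Normal ≥ − 1 y ≤ 1 Z of BMI".
- Determination of sample size states that the trial was sized to "obtain a standard size of the effect of 0.2 on the BMI z-score", "with a power of 0.8, a significance of 5% and an inter-cluster coefficient of variance of 0.00012". It arrives at 140 children per school and at least 11 schools (1540 children), raised to 12 schools and 1680 children before allowance for loss. No category rate or difference in rates is given.
- The abstract says effectiveness will be evaluated through body fat percentage, BMI and BMI z-score, all continuous.
- Data analysis assigns chi-square tests to categorical variables, adds logistic models for change in the result variables, and assigns multilevel mixed-effects regression to continuous variables. It does not say which of these is the primary analysis.
- The single-component arms have their own primaries: for AFSO "Fitness as measured in the lower body by the distance" (jump) together with grip strength, and for KSEAN "Intake of foods measured as consumed and not consumed". Yet the first study hypothesis is that the combination controls obesity better than either component alone.

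**The concern.** The type of the primary variable decides both its analysis and its power. Here the outcome section fixes one type and the sample size section another. Cutting a continuous score into classes discards information, so a sample just large enough for a 0.2 SD shift in the mean will be too small to detect the same shift through the classes. If the categories are what is tested, a true effect of the planned size could well be missed, while readers would believe the trial had 80% power to find it.

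Two related faults are on the page. Read literally, the classes overlap above z = 2, and a child with z below −1 belongs to none. And nutritional status is declared primary only under the combined arm, so the headline comparison of the combination with each component has no endpoint declared primary for all the arms compared.

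**Working it through.** **Inputs from the document.** Standardised effect 0.2 on BMI z-score; power 0.80; significance 5% (sidedness not stated, two-sided taken); intracluster correlation 0.00012; 140 children per school; 12 schools and 1680 children before loss (Determination of sample size). Four arms with one school each in three regions (Design), so 3 × 140 = 420 per arm. The only obesity rate given is 25.3%, for 6-year-olds in year one in 2013 (Background).

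**Assumptions added.** A two-arm contrast, BMI z normally distributed with SD 1, and a uniform shift of 0.2 SD.

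**1. The plan's own figure.** Per arm, n = 2(1.960 + 0.842)² / 0.2² = 392.4, rounded up to 393. Four arms give 1572, within 2.1% of the stated 1540. The design effect is 1 + 139 × 0.00012 = 1.0167, which raises the total to about 1598. A one-sided 5% test needs only 310 per arm and does not fit. So the stated size is a two-sided calculation on the continuous score.

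**2. Power for BMI z-score.** The effective n per arm is 420 / 1.0167 = 413.1. Power = Φ(0.2 × √(413.1/2) − 1.960) = Φ(2.874 − 1.960) = 0.820. With 1540 children (385 per arm) it is 0.786.

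**3. The same shift tested as obese versus not.** With control rate p₁, the shifted rate is p₂ = Φ(Φ⁻¹(p₁) − 0.2). For p₁ = 0.253, p₂ = Φ(−0.665 − 0.2) = 0.1935.

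- Difference: 0.253 − 0.1935 = 0.0595
- Standard error under no difference: √(2 × 0.2233 × 0.7767 / 413.1) = 0.02898
- Standard error under the alternative: √((0.253 × 0.747 + 0.1935 × 0.8065) / 413.1) = 0.02890
- Power = Φ((0.0595 − 1.960 × 0.02898) / 0.02890) = Φ(0.094) = 0.537

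For 80% power this contrast needs 768 per arm, or 781 with the design effect (4 × 781 = 3124 in all).

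**4. Range over the control rate (420 per arm, design effect included).**

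| Control rate | Shifted rate | Power |
|---|---|---|
| 15% | 10.8% | 43% |
| 20% | 14.9% | 49% |
| 25.3% | 19.35% | 54% |
| 30% | 23.4% | 57% |
| 40% | 32.5% | 61% |
| 50% | 42.1% | 63% |

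**5. Range over the test.** Setting 25.3% above z = 2 with SD 1 puts the control mean at 1.335.

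| Test of the same 0.2 SD shift | Power |
|---|---|
| Obese versus not | 54% |
| Overweight or obese versus not (63.1% to 55.4%) | 62% |
| Chi-square, four classes (with one below −1) | 57% |
| Chi-square, three classes (below −1 merged with normal) | 62% |
| Ordinal (Wilcoxon-type), three classes | 72% |
| Continuous BMI z-score | 82% |

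An SD of 1.2 or 1.3, with the effect kept at 0.2 SD, leaves the chi-square results at 58% to 61% and the ordinal result at 70% to 71%.

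**6. Size of the gap below −1.** Under the same model Φ(−1 − 1.335) = 0.0098 of control children fall below −1, and 0.0164 after the shift. That is roughly 1% to 2% of children.

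**The case against.** The best defence is that the trial always meant BMI z-score. The abstract lists it, the sample size uses it, and the analysis section has a multilevel model for continuous outcomes. On that reading power is about 82% and the fault is one of naming. This is a fair reading, and it is why no single power figure can be pinned on the plan. It does not remove the point: the section that declares the primary variable defines it by classes alone, and the text must say which is meant.

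Four stronger readings are tempting, and the document does not support them.

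- **That the primary test has 54% power.** No primary test is fixed. The 54% depends on an obese/not-obese contrast, on a national rate in 6-year-olds serving as the control rate for children aged 6 to 10 at 20 months, and on a uniform normal shift. It is one scenario.
- **That power is only 35% to 41% once the number of schools is counted.** Those figures come from reading obese versus not against a t distribution on 4 or 6 degrees of freedom. Treated the same way, BMI z-score falls to about 58% to 67%. Few schools is a separate problem that affects both outcomes.
- **That children below −1 drop out of the intention-to-treat analysis.** Nothing says so, and in an obese/not-obese test they count as not obese. The overlap above 2 also has a natural reading, with overweight running from 1 to 2.
- **That fitness and food intake are the wrong primaries for the component arms.** The second and third hypotheses name dietary behaviour and fitness as the route to managing obesity, and grip strength has its own sample size calculation. What stands is narrower: comparing the combination with its components on obesity needs one common endpoint.

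**Conclusion.** The mismatch holds. The stated 80% power belongs to continuous BMI z-score (about 82% at 420 per arm on the plan's inputs), not to the categorical variable declared primary. For the same 0.2 SD shift, every categorical test examined falls short of 80%: about 43% to 63% for one cut-off at control rates of 15% to 50%, 57% to 62% for chi-square on three or four classes, and at most about 72% for an ordinal test. These figures assume a two-sided 5% level, a normal score shifted uniformly, a two-arm contrast and the plan's very small intracluster correlation. The chi-square and ordinal figures also take 25.3% as the control obesity rate. The direction does not depend on which of these tests is chosen, but the exact size does. The faults in the class definitions are real, though numerically small.

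**What to change.** Name BMI z-score at t4 (20 months) as the primary outcome for the obesity comparison across all four modes, analysed with the multilevel mixed-effects model already in Data analysis. Naming t4 also settles what is meant by the end of a two-year intervention, since the last measurement is at 20 months and month 24 is for reporting only. Make nutritional status secondary, with exclusive and exhaustive classes: overweight above 1 and up to 2, obese above 2, normal as now, and a class below −1. Fitness and food intake may stay as component-specific outcomes.

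If the categories are to remain primary, name the test, state the control rate assumed, and restate the power for that test.

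No new data are needed, because weight and height are measured at every visit. The cost lies in presentation and disclosure. Prevalence becomes a secondary message, and the clarification must be reported with its date. Recruitment was in March 2014 and t4 comes 20 months after baseline, so on the stated schedule final measurements would precede the article's publication in December 2016. The clarification should therefore say whether it was made before outcome data were seen.
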